## Methods/design

### Study setting

This parallel randomized controlled clinical trial will be conducted at Third Affiliated Hospital of Henan University of Chinese Medicine, Henan Province, China, according to the principles outlined in Consolidated Standards of Reporting Trials (CONSORT), Standards for Reporting Interventions in Acupuncture Clinical Trials (STRICTA), and Standard Protocol Items: recommendations for Interventional Trials (SPIRIT) guidelines (Figure 1). Ninety full-time college students will be randomly and equally assigned to acupuncture, running, and Tai Chi groups. The allocated intervention will be conducted for 30 min, 3 times per week on alternating weekdays for a total of 4 weeks (w). The General Procrastination Scale (GPS) will be used as the primary outcome measure, with the Procrastination Assessment Scale for Students (PASS) and Physical Activity Rating Scale 3 (PARS-3) used as secondary outcome measures. Outcome measures will be conducted at baseline (0 w) and after 2 and 4 weeks of intervention. In addition, P300 and N200 will be measured by scalp EEG during the Go/No-go Emotion Detection task and Task Initiation Delay Paradigm (TIDP) to observe the effects of these interventions on cognitive control and error detection abilities.

**Figure 1 F1:**
[figure not shown]
SPIRIT figure for schedule of enrollment, interventions, and assessments. Note: ‘ × ' indicates completed assessments. TIDP, task initiation delay paradigm; GO/No-go, Go/No-go emotional detection paradigm; ERPs, event-related potentials; GPS, general procrastination scale; PASS, procrastination assessment scale for students; PARS-3, physical activity rating scale-3.

### Recruitment

The study will recruit participants with procrastination from the Dongming Road Campus of Henan University of Traditional Chinese Medicine through posters stickers and online advertisements. Candidates who meet the inclusion criteria, do not meet any exclusion criteria, and agree to participate by providing written informed consent will be enrolled until the preset maximum sample size (n = 90) is reached. Additionally, 30 healthy subjects will be recruited as controls. The healthy control group is included to provide normative behavioral and electrophysiological reference values, rather than to serve as a treatment control for intervention effects.

#### Inclusion criteria

Preset study inclusion criteria are as follows:

Full-time university student;GPS score ≥ 70 points;No psychotropic drug intake or related acupuncture treatment within the past 30 days;Providing informed consent.

#### Exclusion criteria

The following exclusion criteria will be applied during enrolment:

Organic mental disorders, diseases related to surgical history, and current use of psychoactive substances;Family history of other mental illnesses such as dementia, schizophrenia, mania, and addiction;Impaired consciousness or agitation, or otherwise unable to cooperate with task completion or EEG collection;Skin lesions or skin diseases.

#### Dropout criteria

In addition, we will preset dropout criteria as follows:

Mistaken admission (subsequently found not to meet one or more inclusion criteria or found to meet one or more exclusion criteria);Poor compliance or voluntary withdrawal;Onset of treatments prohibited by this protocol, or changing treatment methods during the program;Serious adverse reactions to the interventions.

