##### Dropped cases will be handled as follows:

After drop out, the attending doctor will try to contact the subject by phone or letter to obtain the reason(s) and schedule a final visit if possible to complete the assessable items.For cases that quit the trial due to adverse reactions or ineffective treatment, the attending doctor will take appropriate measures in accordance with current treatment guidelines.The “Summary of Treatment Completion” and “Clinical Trial Completion” in the CRF will be filled in.All excluded and dropped cases will be included in the intention-to-treat analysis after the trial ends.

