### Intervention

#### Acupuncture group

All acupuncture practitioners participating in this study are licensed traditional Chinese medicine acupuncture therapists with at least 5 years of clinical experience. They will receive uniform training to master the study protocol and thereby reduce treatment variation. Based on our clinical experience, the following acupoints will be selected for this study: Baihui (GV20), Sishencong (EX-HN1), Zusanli (ST36), and Neiguan (PC6). Acupoint positioning will be conducted according to the 2006 National Standard of the People's Republic of China (GB/T 12346-2006) “Acupoint Name and Positioning” as follows: Baihui (GV20), 5 inches below the hairline; Sishen cong Acupoint (EX-HN1), 4 acupoints located 1 inch to the left and right of the Baihui Acupoint; Zusanli acupoint (ST36), located on the anterolateral side of the Dubi acupoint (ST35), 3 inches below the Dubi and one transverse finger width outside the anterior tibial crest; Neiguan (PC6): in the forearm area, 2 inches above the transverse stria of the carpal palmes, between the palmaris longus tendon and the flexor carpi radialis tendon.

Acupuncture operation will be conducted according to “Acupuncture and Moxibustion” edited by Liang FanRong, the textbook of the 13th 5-Year Plan. Briefly, the participant will be positioned in the sitting or supine position. After routine skin disinfection, φ0.25 mm × 25 mm stainless steel needles will be inserted, and left in position for 30 min. Needles removal and post-intervention care will follow standard institutional safety procedures.

Compliance is defined as an attendance rate ≥80% (≥9 sessions completed over 4 weeks). Participants with attendance < 80% will not be excluded from the ITT analysis but will be excluded from the PP analysis.

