#### Running group

The running group will perform moderate-intensity continuous training (MICT) according to American College of Sports Medicine (ACSM) guidelines with precise exercise intensity control according to heart rate reserve (HRR) calculations. Maximum heart rate (HRmax) and anaerobic threshold heart rate (ATHR) will be measured for each participant at baseline using a standard treadmill escalating load test (Bruce protocol), and HRR calculated as HRR = HRmax-Resting Heart Rate (RHR). Training intensity will be maintained in the 60–75% HRR range (equivalent to 70–85% of maximum heart rate) by real-time monitoring using a wearable heart rate monitor. Participants will run 3 times per week for 30 min, including 5 min of brisk warm-up walking (heart rate controlled at 40–50% of HRR), 20 min of target intensity running, and 5 min of cold walking and dynamic stretching. The training time will be fixed at 17:00–18:30 every day to reduce the impacts of circadian factors. The dual-track “check-in + sports data upload” system will be used to supervise the activity, and participants will wear sports bracelets to record running distance, pace, and heart rate data. These data will be submitted weekly. Compliance is defined as an attendance rate ≥80% (≥9 sessions completed over 4 weeks). Participants with attendance < 80% will not be excluded from the intention-to-treat (ITT) analysis but will be excluded from the per-protocol (PP) analysis.

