#### Tai Chi group

The simplified 24-style Tai Chi will be used as a second intervention exercise as it is concise and easy to master by novices while retaining the core essentials of traditional Tai Chi. It consists of 24 movements, such as “starting momentum”, “wild horse mane”, and “white crane wings”, with a drill duration of about 8–10 min, and a total session duration of about 30 min including warm-up, practice, and the closing posture of Tai Chi. Training will be delivered 3 times per week at 17:00–18:30 both for convenience and temporal consistency with the other interventions. Each training session will be divided into three phases: a 5-min warm-up (including neck rotation, joint movement, lunge leg press), 20-min Tai Chi routine practice (including two repetitions), and the 5-min closing (pranayama relaxation, tapping the meridians). The selected Tai Chi training intensity aims for “slight sweating, steady breathing, and consistent movements”, and will be monitored by the Subjective Fatigue Scale (RPE), which requires the participants to maintain an RPE score of 11–13 (slightly tired but sustainable) during the training. At the same time, participants will use a wearable device to ensure that average heart rate remains at 50–65% of HRmax. The Tai Chi intervention will adopt “online + offline” dual supervision. During offline training, the coach will observe the participants' movements on video submitted via an online video application, from which the coach will provide remote guidance. Attendance will be summarized monthly. Compliance is defined as an attendance rate ≥80% (≥9 sessions completed over 4 weeks); if attendance is < 80%, reasons will be documented and participants will be encouraged to improve, with reasons recorded for sensitivity analysis.

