### Data analysis

The primary analysis will be conducted using a linear mixed-effects model, with fixed effects for group (acupuncture, running, Tai Chi), time (baseline, week 2, week 4), and their interaction, and a random intercept for participants to account for within-subject correlation due to repeated measurements. Baseline GPS score, age, sex, and baseline ERP indices will be included as covariates to control for inter-individual variability in procrastination-related traits.

This mixed-effects modeling framework constitutes the primary analytic strategy and will be implemented under the intention-to-treat (ITT) principle, allowing inclusion of all available observations without imputing missing values, under a missing-at-random assumption.

Prior to model fitting, distributional characteristics of continuous variables will be assessed using the Shapiro–Wilk test. Descriptive comparisons of baseline demographic and clinical characteristics will be performed using analysis of variance (ANOVA) or the Kruskal–Wallis test for continuous variables, and chi-square or Fisher's exact tests for categorical variables, as appropriate, to ensure baseline comparability between groups.

Secondary and exploratory analyses may include pairwise comparisons or non-parametric tests (e.g., Mann–Whitney *U*-test or Wilcoxon signed-rank test) where appropriate for specific outcomes or sensitivity checks. For outcomes with repeated measurements that meet parametric assumptions, repeated-measures ANOVA may be used as a supplementary analysis; otherwise, non-parametric alternatives such as the Friedman test will be applied.

Sensitivity analyses will be conducted to evaluate the robustness of the primary findings, including per-protocol analyses restricted to participants with adherence ≥80% and models incorporating adherence (number of completed sessions) as a continuous covariate.

For secondary outcomes and exploratory ERP analyses involving multiple indices or task conditions, false discovery rate (FDR) correction will be applied within pre-defined families of related comparisons. Statistical significance will be defined as a two-sided *P*-value < 0.05. All analyses will be performed using PASS 18.0, with statistical consultation provided by an institutional biostatistician.

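### The plan does not settle whether poor compliers stay in scheduled assessment, so week-4 GPS may be missing for a reason related to outcome, and no listed analysis tests this

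*Protocol article*

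**What the plan says.** Four parts of the protocol article bear on what happens to a participant who attends poorly.

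- **Dropout criteria.** The list includes "Poor compliance or voluntary withdrawal", alongside mistaken admission, prohibited or changed treatment, and serious adverse reactions. It gives no attendance threshold and no time point.
- **Handling of dropped cases.** The attending doctor contacts the person for reasons and will "schedule a final visit if possible to complete the assessable items". The same list ends: "All excluded and dropped cases will be included in the intention-to-treat analysis after the trial ends".
- **Intervention sections.** For acupuncture: "Participants with attendance < 80% will not be excluded from the ITT analysis but will be excluded from the PP analysis". The running section says the same. The Tai Chi section differs: "if attendance is < 80%, reasons will be documented and participants will be encouraged to improve". It records the reasons for use in a sensitivity analysis and does not mention the two analysis sets. The threshold in the acupuncture section reads: "Compliance is defined as an attendance rate ≥80% (≥9 sessions completed over 4 weeks"; the other two arms use the same one.
- **Data analysis.** The primary model is a linear mixed model on GPS at baseline, week 2 and week 4. It uses all available observations, imputes nothing and assumes missing at random. The sensitivity analyses are a per-protocol analysis and "models incorporating adherence (number of completed sessions) as a continuous covariate".

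**The concern.** Under the dropout list, a poor complier leaves the trial. Under the intervention sections, a low attender is either retained for analysis or urged to carry on. Study staff cannot tell from the text whether such a person is still due a GPS at week 4.

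This matters because membership of the intention-to-treat set does not supply an outcome. Someone in the set without a week-4 score is represented at week 4 only by what the model predicts from earlier scores. In a trial of people selected for high procrastination, failing to turn up is plausibly related to the outcome. If those who are dropped do worse than their earlier scores predict, their arm's week-4 mean looks better than it is, and an arm that loses more of them gains an advantage in the comparison.

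**Working it through.** **1. The protocol's own loss figure.** The Sample size section needs 27 per group (Cohen's f = 0.40, three groups, two-sided α = 0.05, power 0.90) and allows about 10% dropout: 27 / (1 − 0.10) = 30 per group, as stated. One-way ANOVA power at 81 analysed is 0.895, close to the stated 0.90. This allowance protects power. It does not protect against bias from who is lost.

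**2. The passages side by side.**

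| Question | Dropout criteria and handling | Intervention sections |
|---|---|---|
| Is a poor complier dropped? | Yes, no threshold | Acupuncture, running: retained in intention-to-treat. Tai Chi: encouraged to improve |
| In the intention-to-treat set? | Yes | Acupuncture, running: yes. Tai Chi: not stated |
| Is a week-4 GPS required? | No: one visit if possible, no week fixed | Not stated |

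The conflict is in the first row and the gap in the third. The second row holds no contradiction.

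**3. Who counts as a poor complier.** The schedule is 3 × 4 = 12 sessions, and 80% of 12 is 9.6. Nine sessions is 9/12 = 75% and ten is 10/12 = 83.3%. A participant with nine sessions is compliant by the count and non-compliant by the percentage. This is a separate slip, but it blurs the boundary further.

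**4. What the model can recover.** The inputs below are assumptions except the correlation, which is the 4-week test–retest value of 0.756 in the Primary outcome section, taken to apply between any two visits.

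- p = share of an arm who are poor compliers: 0.10 to 0.30.
- d = how much worse they are at week 4: 4 or 8 GPS points.
- s = share of d already visible at week 2: 0, 0.5 or 1.
- SD = 7.

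With baseline and week 2 observed, the coefficient on week 2 in predicting week 4 is 0.756 / (1 + 0.756) = 0.431. With no week-4 retrieval, the arm mean is too favourable by p × d × (1 − 0.431 × s):

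| p | d | s = 0 | s = 0.5 | s = 1 |
|---|---|---|---|---|
| 0.10 | 4 | 0.40 | 0.31 | 0.23 |
| 0.10 | 8 | 0.80 | 0.63 | 0.46 |
| 0.20 | 4 | 0.80 | 0.63 | 0.46 |
| 0.20 | 8 | 1.60 | 1.26 | 0.91 |
| 0.30 | 4 | 1.20 | 0.94 | 0.68 |
| 0.30 | 8 | 2.40 | 1.88 | 1.37 |

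A simulation of 200,000 participants per setting agreed to within 0.02. It also gave about 0.1 to 1.0 points when half the missing week-4 scores were retrieved, and 0 when all were. It used a likelihood-type estimate within one arm, without the protocol's covariates, so it illustrates the primary model and does not replicate it.

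**5. From one arm to the contrast.** The between-arm bias is the difference between arms. With d = 8 and s = 0, 20% in one arm against 10% in another gives 1.60 − 0.80 = 0.80 points; equal shares give 0.

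**6. What the sensitivity analyses test.** The per-protocol analysis removes low attenders altogether. The adherence model conditions on sessions completed, a post-randomisation variable that the assigned intervention may affect. Neither changes the assumption about unseen week-4 scores.

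**The case against.** The strongest reply is that nothing in the article says being dropped ends GPS assessment. The handling rules try to retrieve outcomes and keep dropped cases in the intention-to-treat set. Keeping low attenders in that set, and urging them on in the Tai Chi arm, reads most naturally as their being followed. Poor compliance, having no threshold, need not mean attendance under 80%. A mixed model under missing at random is a standard primary choice. Sensitivity analyses beyond it are often left to a statistical analysis plan, which is not shown here.

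Much of this stands, and it limits the point in four ways.

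- A reader might infer that the plan is certain to produce informative missing data. It does not: retrieval is attempted, so this is a risk.
- A reader might infer that the mixed model cannot deal with it. That is too strong: the model is valid if missingness depends only on observed data, such as baseline and week-2 GPS.
- A reader might suppose a much larger bias, for example by taking dropped participants to be 10 points worse than the model predicts. With SD 7 and correlation 0.756, the residual SD is 7 × √(1 − 0.756²) = 4.6 given one earlier score, so 10 points is over 2 residual SDs for the average poor complier. Nor can the bias be set against one design difference: f = 0.40 fixes no pairwise gap unless a pattern of means is assumed.
- A reader might infer differential loss between arms. The interventions differ in kind, but all arms have three 30-minute sessions a week for four weeks and the same attendance threshold. The documents give no expected rate of poor compliance by arm.

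What the reply does not remove is the conflict over whether a poor complier is dropped, or the absence of any requirement for a week-4 score once someone is.

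**Conclusion.** The point holds as a contradiction to reconcile and a risk of bias to close off. The dropout criteria and the intervention sections disagree on whether poor compliers leave. The handling rules keep them in the analysis set without securing the week-4 outcome, and the listed sensitivity analyses do not probe the missing-at-random assumption.

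The size cannot be established from the documents, which give neither the rate of poor compliance nor how such participants fare. The range of about 0.2 to 2.4 GPS points is for one arm's mean. It rests on the assumed shares and outcome gaps, on poor compliers doing worse, and on no retrieval. It falls to 0 with full retrieval, and it cancels in the contrast if the arms are affected equally.

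**What to change.** 1. Reconcile the dropout criteria, the handling of dropped cases and the three intervention sections. State that poor compliance, mistaken admission or stopping the intervention does not end outcome assessment. When an intervention should be stopped is a separate matter for the investigators.
2. Collect GPS and PASS at weeks 2 and 4 from everyone randomised unless consent is withdrawn, in place of one undated visit.
3. Add a delta-adjusted (missing-not-at-random) sensitivity analysis of the week-4 contrasts, unless the statistical analysis plan already contains one. The adherence-covariate model need not be deleted, but it should not be presented as a check on missing data.

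The cost is protocol wording, one extra analysis and minor contact effort for two short questionnaires from a few participants. It should be done before anyone is dropped, because a missed week-4 score cannot be collected later.

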##### Dropped cases will be handled as follows:

After drop out, the attending doctor will try to contact the subject by phone or letter to obtain the reason(s) and schedule a final visit if possible to complete the assessable items.For cases that quit the trial due to adverse reactions or ineffective treatment, the attending doctor will take appropriate measures in accordance with current treatment guidelines.The “Summary of Treatment Completion” and “Clinical Trial Completion” in the CRF will be filled in.All excluded and dropped cases will be included in the intention-to-treat analysis after the trial ends.

### Randomization

Participants will be allocated to the three intervention groups based on random numbers generated using SPSS 21.0. Allocation numbers will be sealed in opaque envelopes labeled with a serial number. During the clinical implementation, the order in which eligible cases are included in the trial will correspond to the serial number on the envelope, and the envelopes will be opened in order and participants grouped according to the prompts on random number cards.

### Blinding

Blinding of participants to group allocation is not possible due to the active nature of the interventions. Therefore, we will institute three-way blinding of group allocation among administers of psychological assessments, recorders of electroencephalographic data, and operators responsible for subsequent analyses.

### Intervention

#### Acupuncture group

All acupuncture practitioners participating in this study are licensed traditional Chinese medicine acupuncture therapists with at least 5 years of clinical experience. They will receive uniform training to master the study protocol and thereby reduce treatment variation. Based on our clinical experience, the following acupoints will be selected for this study: Baihui (GV20), Sishencong (EX-HN1), Zusanli (ST36), and Neiguan (PC6). Acupoint positioning will be conducted according to the 2006 National Standard of the People's Republic of China (GB/T 12346-2006) “Acupoint Name and Positioning” as follows: Baihui (GV20), 5 inches below the hairline; Sishen cong Acupoint (EX-HN1), 4 acupoints located 1 inch to the left and right of the Baihui Acupoint; Zusanli acupoint (ST36), located on the anterolateral side of the Dubi acupoint (ST35), 3 inches below the Dubi and one transverse finger width outside the anterior tibial crest; Neiguan (PC6): in the forearm area, 2 inches above the transverse stria of the carpal palmes, between the palmaris longus tendon and the flexor carpi radialis tendon.

Acupuncture operation will be conducted according to “Acupuncture and Moxibustion” edited by Liang FanRong, the textbook of the 13th 5-Year Plan. Briefly, the participant will be positioned in the sitting or supine position. After routine skin disinfection, φ0.25 mm × 25 mm stainless steel needles will be inserted, and left in position for 30 min. Needles removal and post-intervention care will follow standard institutional safety procedures.

Compliance is defined as an attendance rate ≥80% (≥9 sessions completed over 4 weeks). Participants with attendance < 80% will not be excluded from the ITT analysis but will be excluded from the PP analysis.

#### Running group

The running group will perform moderate-intensity continuous training (MICT) according to American College of Sports Medicine (ACSM) guidelines with precise exercise intensity control according to heart rate reserve (HRR) calculations. Maximum heart rate (HRmax) and anaerobic threshold heart rate (ATHR) will be measured for each participant at baseline using a standard treadmill escalating load test (Bruce protocol), and HRR calculated as HRR = HRmax-Resting Heart Rate (RHR). Training intensity will be maintained in the 60–75% HRR range (equivalent to 70–85% of maximum heart rate) by real-time monitoring using a wearable heart rate monitor. Participants will run 3 times per week for 30 min, including 5 min of brisk warm-up walking (heart rate controlled at 40–50% of HRR), 20 min of target intensity running, and 5 min of cold walking and dynamic stretching. The training time will be fixed at 17:00–18:30 every day to reduce the impacts of circadian factors. The dual-track “check-in + sports data upload” system will be used to supervise the activity, and participants will wear sports bracelets to record running distance, pace, and heart rate data. These data will be submitted weekly. Compliance is defined as an attendance rate ≥80% (≥9 sessions completed over 4 weeks). Participants with attendance < 80% will not be excluded from the intention-to-treat (ITT) analysis but will be excluded from the per-protocol (PP) analysis.

